# **6.0 Randomization Scheme**

No randomization will be necessary. Participants will serve as their own controls, and therefore will all receive supervised RT. The 12-week control period will be done before the RT intervention to ensure that results are not confounded by a detraining effect. In addition, long-term cognitive benefits after exercise interventions have been found up to two years follow-up [88, 89].

# **7.0 Intervention**

Participants will be encouraged to continue normal activities of daily living and eating routines outside the resistance training protocol of the present study. Participants may be contacted for scheduling, but will not be monitored during the control period. All participants will be asked to abstain from strenuous activity 24 hours prior to ALL study visits. During the training workouts and testing days, participants will be allowed to drink water ad libitum.

## **7.1 Periodized RT Intervention**

A periodized and progressive total-body resistance training program emphasizing development of lower and upper body strength will be performed 3 days/week for 12 weeks. Each training session will be supervised at the CERC, will be approximately 1 hour in duration, and will begin with a 5-minute warm-up of light bodyweight resistance exercises and stretching exercises (if needed). Throughout the training program, sets/exercise will range from 3-5 and repetitions from 6-4. The rest interval between sets will be 60 seconds for all exercises. Training logbooks will be kept for each participant and will detail training loads, sets, and repetitions for each exercise for every training session. All training loads, sets, and repetitions performed by the participants will be recorded by study investigators.

Exercise order will be controlled by the investigators during all training sessions. Throughout the entire 12-week resistance training program, all sets will be performed maximally for the assigned number of repetitions. The training loads used will be individually progressed in a safe and effective manner, in order to employ a progressive overload/challenge to the neuromuscular system and elicit the greatest training-induced neuromuscular adaptations possible. Static stretching exercises will be performed at the end of every RT session.

Sample Weekly RT Intervention Protocol

| Day 1 | Day 2 | Day 3 | Day 4 | Day 5 | Day 6 | Day 7 |
| --- | --- | --- | --- | --- | --- | --- |
| RT (CERC) | Rest | RT (CERC) | Rest | RT (CERC) | Rest | Rest |

# **8.0 Assessment of Efficacy and Safety**

Side-effects will be monitored. Participants will be asked about the following side-effects at the beginning of each testing and training session:

- energy level
- muscle fatigue and soreness
- joint stiffness
- pulls/strains
- sleep quality

Other side-effects will be documented if presented by the participant: everyday strength, everyday energy levels, appetite, thirst, sleep quality, or participation in strenuous activity or exercise within 24 hours prior to the visit.

Adverse events will be documented by the PI and the IRB will be notified of any severe adverse events (SAEs) within 24 hours of study team becoming aware of such SAE event. Adverse events (AE) that may be associated with this study include injury or excessive soreness from testing or the resistance training program. No serious adverse events (SAEs) are expected with this study.

No long-term toxicities are to be monitored after completion of the study. No long-term adverse side effects have been associated with resistance training.

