## **16.1 Risk/Benefit Assessment:**

Potential risks: Participants might experience exercise-related fatigue, dizziness, nausea, strains, and/or soreness. All participants will be supervised through proper warm-up, cool-down, and exercise instruction by an exercise specialist to minimize these discomforts.

There is a chance the subject may experience slight discomfort or nausea during the blood draw. Immediate side effects may include pain or discomfort associated with needle stick as well as possibility of bruising and nerve aggravation at the blood draw site in the antecubital space of the arm. The risks of two blood draws (baseline and post-intervention) are greater than minimal. However, the amount of blood (~20mL per draw) that will be taken per blood draw at only one site on the participant’s body is small.

Potential benefits: There are no immediate benefits to the subject. However, the participants will have the benefit of learning about resistance training program design, their physical fitness, and physical fitness testing, as well as experiencing improvements in overall health due to an exercise intervention. Potential study participants are encouraged to participate if they are interested in research and to further their understanding of resistance training, physical fitness and brain health.

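### Side-effects are asked about only at the start of sessions, so delayed effects of two of the three strength-test visits are not actively solicited in time, and two named exercise risks are not on the list

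*Protocol*

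**What the plan says.** Section 8.0 of the protocol sets both the time and the content of active questioning: "Participants will be asked about the following side-effects at the beginning of each testing and training session". The list has five items: energy, muscle fatigue or soreness, stiff joints, pulls or strains, and sleep. A second list is passive: "Other side-effects will be documented if presented by the participant". Strenuous activity in the 24 hours before a visit is on this passive list. The section also has the principal investigator document adverse events, and it states what is expected: "Adverse events (AE) that may be associated with this study include injury or excessive soreness from testing or the resistance training program".

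Other sections bear on this:

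- Section 7.0, on the control period: "Participants may be contacted for scheduling, but will not be monitored during the control period".
- Section 7.0, on preparation for visits: "All participants will be asked to abstain from strenuous activity 24 hours prior to ALL study visits".
- Section 16.1, on exercise risks: "Participants might experience exercise-related fatigue, dizziness, nausea, strains, and/or soreness".
- Sections 3.0, 9.3 and 9.10 place the 4-6RM strength tests at Visits 4, 6 and 8. Visit 4 is the last baseline visit and Visit 8 the last visit of the study.

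**The concern.** Soreness and strain from a maximal test can appear after the participant has gone home. A question put only at the start of a session finds them at the next session, so the scheme works only where that session follows soon. After two of the three strength-test visits it does not. One of these is Visit 4, the first maximal test in people whom Section 5.2 selects for having done no regular heavy resistance training in the past six months.

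There are two smaller mismatches. The asked list leaves out symptoms that Section 16.1 names as risks. And the protocol sets a 24-hour abstention but does not ask whether it was kept, including at Visits 2, 5 and 7, where the MRI scans supply the primary outcome.

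At stake is how completely the trial records a kind of event that it says it expects, and whether a condition it sets for its measurements can be verified afterwards.

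**Working it through.** **Timing.** The inputs are the visit order in Section 3.0 and the calendar in Section 9.10: baseline in weeks 1-2, control in weeks 3-14, pre-tests in week 15, training from week 16. Let week *w* run from day 7(*w* − 1) + 1 to day 7*w*.

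The control period reproduces: 14 − 3 + 1 = 12 weeks.

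*Visit 4 to the next question (Visit 5).*
- Shortest gap: Visit 4 on the last day of week 2 (day 14) and Visit 5 on the first day of week 15 (7 × 14 + 1 = day 99). 99 − 14 = 85 days, and 85/7 = 12.1 weeks.
- Longest gap: Section 9.3 puts familiarization about one week before strength testing. With Visit 2 on day 1 and familiarization on day 2, Visit 4 falls no earlier than about day 9. Visit 5 falls no later than day 104, which leaves day 105 for Visit 6. 104 − 9 = 95 days, and 95/7 = 13.6 weeks.

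*Visit 6 to the next question (first training session, week 16).*
- Shortest gap: day 105 to day 106, 1 day.
- Longest gap: day 100 to day 112, 12 days.
- This visit is covered.

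*Visit 8 to the next question.* No later session exists, so nothing is asked.

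Two of the three strength-test visits therefore lack a timely question: one is asked about 12.1 to 13.6 weeks later, the other not at all.

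**Content.** The five exercise risks in Section 16.1 compare with the asked list in Section 8.0 as follows:

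| Risk in 16.1 | On the asked list in 8.0? |
| --- | --- |
| Fatigue | Yes (muscle fatigue; energy) |
| Strains | Yes |
| Soreness | Yes |
| Dizziness | No |
| Nausea | No |

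Two of five are missing, and neither is on the passive list. Section 16.1 also mentions, for blood draws, the "possibility of bruising and nerve aggravation at the blood draw site", which is on neither list. Sections 9.5 and 16.1 count draws at baseline and post-intervention, which are Visits 4 and 8, the two visits without a timely question.

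**24-hour abstention.** Section 7.0 asks for it before every visit. Section 8.0 records a breach only if the participant raises it. A blank entry could mean that the rule was kept or that nobody asked.

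**Number of contacts.** One after each of two visits for 23 participants: 23 × 2 = 46. If the roughly 3 dropouts allowed for in Section 13.2 all leave between Visits 4 and 8: 23 + 20 = 43.

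**The case against.** The best defence is that active questioning is not the only route. Complaints that participants volunteer are documented, the principal investigator documents adverse events, and severe events go to the IRB within 24 hours of the team learning of them. An injury reported after Visit 4 or Visit 8 would therefore be recorded. Training is supervised, so staff would probably see acute dizziness or nausea. Visit 4 is not the first contact with the equipment, because a familiarization session covers all seven exercises and Visit 4 itself opens with the questions. By Visit 8 participants have had up to 36 supervised sessions in a similar repetition range. The main exposure, training, is queried at every session.

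Most of this stands, and it limits the point. What it does not cover is delayed, minor soreness or strain that the participant does not think to report, which is what a structured question is for.

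A reader might go further in four ways that the protocol does not support:

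- *Harm from these visits is simply missed.* It is not actively asked about, but the passive routes remain open.
- *The trial would wrongly declare the programme safe.* No hypothesis or objective concerns safety, and Section 13.1 describes no safety analysis from which to conclude it.
- *Unrecorded exercise distorts cerebral blood flow or compliance.* The protocol gives neither a frequency of breaches nor the size of any effect. The point is only that adherence cannot be checked.
- *The statement "No long-term toxicities are to be monitored after completion of the study" shows the gap.* It concerns long-term effects and says nothing about the days after a test.

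**Conclusion.** The point holds as a matter of ascertainment. If Section 8.0 is followed exactly, delayed soreness or strain from 2 of the 3 strength-test visits is not actively solicited in time, although the same section expects such events from testing. Two of five named exercise risks are not asked about, and the 24-hour abstention is not checked. The likely result is under-recording of minor events. How much cannot be said, since the protocol gives no event rates.

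The figure of 12.1 to 13.6 weeks rests on the visit order in Section 3.0 and the calendar in Section 9.10. Its upper end also assumes that Visit 4 comes no earlier than about day 9. Section 9.0 says that baseline procedures fall within two weeks before the intervention, which does not fit that calendar. Sections 3.0 and 9.10 are explicit about the order and are used here.

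The effect-size analysis of the primary outcome is unchanged. This is a worthwhile, inexpensive improvement to data collection, not a flaw that threatens the trial's main result.

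**What to change.** In Section 8.0:

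1. Add dizziness and nausea to the asked list, and put the list at the end of each testing and training session as well as the beginning. The end-of-session question serves acute symptoms. It would not find delayed soreness, so item 3 is also needed.
2. Move strenuous activity in the previous 24 hours from the volunteered list to the asked list at every visit, and record the answer.
3. Add one brief phone or e-mail query with the same list a few days after Visit 4 and another a few days after Visit 8.

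In Section 7.0, amend the statement that participants are not monitored during the control period so that it allows the contact after Visit 4.

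The cost is a revised form and, for 23 participants, at most 46 short contacts by existing staff, fewer with attrition. There are two downsides: slightly more minor events will be recorded, and there will be one brief contact early in a control period meant to be ordinary life. The protocol already permits scheduling contact in that period, so the added intrusion is small.

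Visits, training and endpoints do not change.

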# **9.0 Clinical and Laboratory Evaluations**

Assessments performed exclusively to determine eligibility for this study will be done only after obtaining informed consent. All screening procedures must be performed within 30 days prior to registration unless otherwise stated.

Descriptive factors to be collected include age, height, weight, gender, chronic pharmacological treatment (e.g. ACE inhibitors, Statins, Aspirin), treated pathologies (diabetes, hypertension, high cholesterol, anemia), and hormone therapy status.

Measurements will be conducted over two study visits at each of the following time points for all study outcomes:

1. Weeks 1-2 (Baseline)

2. Week 15 (Pre-intervention)

3. Weeks 28-29, 29-30, or 30-31 (Post-intervention)

Each of these 6 study visits are anticipated to take approximately 2.5 hours. In addition, one familiarization session (~1.5 hours) will be performed during baseline testing.

Buffer Period: In the event a subject in the RT group misses a training session during the 12-week intervention (i.e. has not completed all 36 training sessions by the end of study week 15), she/he will be allowed to complete missed sessions during a 2-week buffer period following the 12-week intervention. A maximum of 6 sessions (3 per week) will be allowed during this period.

All baseline study procedures will be conducted within 2 weeks prior to the start of the intervention, and all post-test study procedures will be conducted within 2 weeks after the end of the intervention (Section 9.10, Study Calendar).

## **9.1 MRI Scan**

MRI is not invasive, and it does not expose participants to treatments with energy such as X-rays or CT scans do. Many people have been safely studied using MRI techniques. While there are no significant risks from MRI as it is to be performed, the MRI procedures are not appropriate for people with pacemakers or metal in their bodies. Prospective participants will be excluded from this study if they have a pacemaker or any metal in their body that cannot be easily removed. The space inside the bore of the MRI machine is just large enough for an average adult. Because the space is so confined, some people feel claustrophobic once inside the MRI machine. If prospective participants have a history of claustrophobia, or experience it during MRI procedures, they will be excluded from the study. Because the MRI scan makes loud noises, we will give participants ear plugs to dampen the sound. They may also experience peripheral stimulation, which will feel like a gentle tap or sensation of mild muscle tremor. If they do not like being in the scanner for any reason, we will immediately stop the experiment.

Participants will be positioned supine in the MRI scanner with foam head and neck support and earplugs for approximately 1 hour. The three noninvasive MRI techniques that will be used in this study are structural MRI, resting state functional MRI (fMRI) [90, 91], and arterial spin labeling (ASL) MRI [92, 93]. Furthermore, a dynamic ASL technique will be used to assess intracranial vascular compliance by synchronizing ASL with the peak systolic and early diastolic phases of the cardiac cycle to measure arterial cerebral blood volume (CBV) at systole and diastole [84]. Vascular compliance will be calculated as the ratio of the change in CBV between systole and diastole to the change in arterial blood pressure between systole and diastole. An MRI compatible cuff sphygmomanometer will be used to measure brachial blood pressure before and after the MRI scans. MRI compatible ECG leads will be placed on the subject’s chest to trigger vascular compliance scans.

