MRI will be performed at The Center for Image Acquisition (CIA) at Stevens Hall for Neuroimaging. The CIA has standard imaging protocols for brain morphometry, resting state brain activity, and cerebral perfusion, including the use of structural MRI, functional MRI (fMRI), and arterial spin labeling (ASL) MRI. Our collaborators at the Laboratory of Neuro Imaging (LONI) have demonstrated the feasibility of conducting an exercise intervention study that includes cognitive testing and MRI in older adults [83]. Furthermore, they have recently developed advanced ASL techniques to non-invasively measure resting CBF, arterial transit time (ATT), and intracranial vascular compliance (VC) [84, 85]. ATT, the duration for blood to travel from large arteries to capillaries, is estimated from multi-delay pseudocontinuous ASL [86]. Obesity (body fat percentage and body mass index) and poor cognitive performance have been found to be inversely related to ATT in patients with coronary artery disease [87]. In addition, by synchronizing ASL with the peak systolic and early diastolic phases of the cardiac cycle, vascular compliance can be calculated as the ratio of the change in cerebral blood volume (CBV) between systole and diastole to the change in arterial blood pressure between systole and diastole [84]. Using this technique, older adults had significantly lower intracranial VC (due to both reduced change in CBV and increased pulse pressure) than young adults. In addition, VC was strongly associated with age, CBF, and aortic stiffness.

The promise of an exercise intervention extends beyond the target disease, having further benefits to the well-being of patients. These types of treatments positively impact fundamental processes of aging, thus reducing the rate of all-cause mortality. Compared to pharmacological treatments, exercise is available at low cost and minimal risk of inducing adverse side effects. Even with moderate benefits to a specific disease like dementia, the global impact on healthcare would be substantial.

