## **2.1 Primary Objective**

To determine whether 12 weeks of periodized RT improves cerebrovascular function in healthy older adults. Cerebrovascular function will be evaluated by resting CBF, intracranial vascular compliance, and arterial transit time (ATT), assessed using ASL MRI techniques. This study will establish response variance and effect sizes while generating preliminary signals of efficacy in an aging related outcome.

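### The blood pressure in the vascular-compliance ratio is read only around the whole MRI session and heart rate at that sequence is not recorded, which adds avoidable error to one of three primary-objective measures

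*Protocol*

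**What the plan says.** Section 2.1 makes compliance one of three measures of the primary objective: "Cerebrovascular function will be evaluated by resting CBF, intracranial vascular compliance, and arterial transit time (ATT), assessed using ASL MRI techniques". Hypothesis 1 in section 1.4 names the same three.

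Section 9.1 defines the measurement. CBV is obtained by "synchronizing ASL with the peak systolic and early diastolic phases of the cardiac cycle". Then: "Vascular compliance will be calculated as the ratio of the change in CBV between systole and diastole to the change in arterial blood pressure", again between systole and diastole. On pressure it says: "An MRI compatible cuff sphygmomanometer will be used to measure brachial blood pressure before and after the MRI scans". The participant lies in the scanner "with foam head and neck support and earplugs for approximately 1 hour", and structural, resting-state and ASL imaging share that session. ECG leads are placed on the chest "to trigger vascular compliance scans".

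Section 1.3 gives the same phases and ratio, taken from a cited dynamic-ASL technique. It explains lower compliance in older adults as "due to both reduced change in CBV and increased pulse pressure", so the pressure term is treated there as pulse pressure.

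The model in section 13.1 names period and gender. The only heart-rate recording the protocol describes is during the treadmill test in section 9.8.

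**The concern.** A cuff returns the systolic maximum and the diastolic minimum, and the minimum falls at the end of diastole. The CBV difference stops in early diastole, when pressure is still well above that minimum. The denominator therefore spans a larger pressure fall than the one that produced the CBV change.

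Two things follow beyond a shift in level. First, pulse pressure is the whole denominator, so any difference between pulse pressure at the cuff readings and at the compliance sequence passes straight into the result. Section 9.1 ties neither reading to that sequence. Second, the size of the phase mismatch depends on the length of diastole. A heart-rate change confined to the training period would enter the period contrast as an apparent compliance change, and the protocol provides no resting value at the scan with which to recognise it. In a study whose stated purpose includes estimating response variance and effect sizes, avoidable error in a primary measure is worth removing.

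**Working it through.** **The plan's own figure.** Section 13.2 states a detectable paired effect of d = 0.611 for n = 23, α = 0.05 and power 0.80. A two-sided paired t-test with the noncentral t gives 0.6113. It reproduces, and it does not depend on how compliance is defined.

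**Step 1: a constant phase mismatch.** Let the pressure fall between the two CBV phases be a share s of cuff pulse pressure. Then reported ratio = s × phase-matched ratio. If a person's s is the same at all three visits, that person's contrast

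(post − pre) − (pre − baseline) = post − 2·pre + baseline

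is only rescaled by s, and percentage change is untouched. On assumed values (125–135/75–80 mmHg, 100–112 mmHg at the start of diastole, exponential decay over 0.55–0.60 s, early diastole 0.05–0.15 s in), s is about 0.33 to 0.74. That affects the level far more than the question the trial asks.

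**Step 2: time between cuff and acquisition.** The ratio is inversely proportional to pulse pressure. Taking 55 mmHg as an assumed value, if the mean of the two readings is 3 mmHg above the pulse pressure at the sequence, the ratio changes by 55/58 − 1 = −5.2%. If it is 3 mmHg below, the change is 55/52 − 1 = +5.8%. The 3 mmHg is illustrative; the protocol gives no within-session drift.

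**Step 3: heart rate.** Hold the CBV change, systolic pressure and early-diastolic pressure fixed, and vary only the heart rate (HR). End-diastolic pressure is

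DBP = P∞ + (Pn − P∞)·exp(−(60/HR − 0.32)/τ)

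with assumed systolic pressure 130 mmHg, pressure at the start of diastole Pn = 105 mmHg and systole 0.32 s. The change in the ratio is (130 − DBP at 70 bpm)/(130 − DBP at the new rate) − 1.

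Worked case, P∞ = 0 and τ = 1.5 s:

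| HR (bpm) | DBP (mmHg) | Pulse pressure (mmHg) | Change in ratio from 70 bpm |
|---|---|---|---|
| 70 | 73.4 | 56.6 | – |
| 67 | 71.5 | 58.5 | −3.2% |
| 65 | 70.2 | 59.8 | −5.3% |
| 60 | 66.7 | 63.3 | −10.5% |

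Across τ = 0.4–2.0 s and P∞ = 0–50 mmHg:

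| Fall from 70 bpm | Change in ratio |
|---|---|
| 3 bpm | −2.0% to −3.3% |
| 5 bpm | −3.2% to −5.4% |
| 10 bpm | −6.2% to −10.6% |

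The Step 1 inputs, with systole again 0.32 s, give −2.3% to −4.2% for 3 bpm and −6.2% to −11.0% for 8 bpm. The sign is negative in every run: slower heart rate, longer diastole, wider pulse pressure, lower ratio.

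**The case against.** The strongest reply is that this is the cited technique's own index. Sections 1.3 and 9.1 agree with each other, and section 1.3 reports that the measure separated older from younger adults and tracked age, CBF and aortic stiffness. How the source handles pressure phase and cuff timing cannot be checked here. This stands: the protocol does not contradict itself, and the trigger phases are best left alone, because moving them would give up comparability with the only validation the protocol cites.

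It is also right that a fixed mismatch largely cancels within person (Step 1), and that CBF and ATT do not use the cuff.

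Three stronger readings are tempting and are not supported:

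- **A false positive for training.** A reader might infer that a heart-rate change could manufacture a benefit. The protocol gives no heart-rate change with resistance training, and a fall would lower the ratio, against Hypothesis 1.
- **A large noise figure for the contrast.** A reader might multiply a per-visit drift error by √(1 + 4 + 1) = √6. That assumes independent errors and a drift the protocol does not give. Readings on both sides of a session cancel linear drift for a sequence in the middle, and a settling pattern repeated at each visit cancels because the weights 1, −2, 1 sum to zero. Section 9.1 does not say where the sequence falls, and ordinary cuff error remains wherever the readings are placed.
- **Adjust the primary contrast for heart rate.** If training changes heart rate, it is a post-treatment variable, and adjusting for it may remove part of the effect.

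What the reply does not answer is that the readings could be taken next to the sequence at almost no cost, and that neither their timing nor heart rate at the scan can be recovered later.

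**Conclusion.** The phase and time mismatch is real on the text. That the denominator is pulse pressure is an inference from the cuff and from section 1.3; section 9.1 does not use the term. It is a cheap improvement to a primary-objective measure, not an error that invalidates it.

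Drift between the cuff readings and the compliance sequence is avoidable error of unknown size. The heart-rate effect is conditional: about 2% to 11% lower for a fall of 3 to 10 bpm, on assumed pressures, an assumed decay curve and an assumed heart-rate change. The size depends on that model. The direction would attenuate or hide a benefit, which still matters in a proof-of-concept trial meant to supply effect sizes.

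**What to change.** In section 9.1:

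1. Take the two existing cuff readings immediately before and immediately after the vascular-compliance acquisition, at every visit.
2. Record heart rate during that acquisition from the ECG leads already in place for triggering.
3. Keep the trigger phases of the cited technique, and describe the result as a compliance index, since its pressure term is cuff pulse pressure.

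In the analysis, report heart rate by visit alongside the period contrast for compliance. If a heart-rate-adjusted contrast is given, label it a sensitivity analysis and say that heart rate may itself be affected by training.

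The cost is a pause of a minute or two around one sequence and one extra recorded value per visit. No new equipment is needed.
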